### Rigor

For qualitative implementation data, a second author (EP, RR, LT, MB, or DD) will verify a random 25% of the total codes from the (1) first interview for interact-ABI-lity, (2) first interview for social-ABI-lity, (3) first clinician interview for convers-ABI-lity, and (4) first interview with a person with ABI and their communication partner for convers-ABI-lity. Any discrepancies will be resolved through research team discussion and consensus before the first author (MM) proceeds to code the remaining interviews. Qualitative effectiveness data will be managed by 2 experienced speech-language pathologists through a consensus rating procedure. For quantitative implementation and effectiveness data, a second author (EP, RR, LT, MB, or DD) will review outputs, and the first author (MM) will consult a biostatistician for support as necessary. For quantitative costing data, analysis will be conducted in consultation with a health economist and the clinical research team, with calculation methods, rationales, and references transparently reported. Overall results will be reported according to the Standards for Reporting Implementation Studies [52].

### Participants

#### Inclusion and Exclusion Criteria for Users of interact-ABI-lity and social-ABI-lity

As social-ABI-lity and interact-ABI-lity are publicly available web-based courses, all users of the courses within the sample frame will be included in data collection and analysis of survey and analytic data, with no restrictions of inclusion and exclusion criteria. A minimum of 5 users of the social-ABI-lity course (ie, people with ABI) and interact-ABI-lity courses (ie, communication partners such as paid support workers, friends, and family members) will be invited to participate in further implementation interviews. This number of users interviewed is consistent with the think-aloud methods described in the study design [43], which are used to refine the usability of the courses. The internationally recognized industry standard [53] is for a minimum of 5 users to undergo a formative usability interview evaluation [53], because only so many users are required to identify up to 90% of the usability issues [54] before there are diminishing returns for the product cycle [53]. However, a maximum variation sample of these interviewees will be sought if and where possible.

If people with ABI completed the social-ABI-lity course with the assistance of a friend, partner, family member, or other individual, this person will also be invited through the course user to be interviewed together or individually, depending on individual preference or availability. Therefore, interview participants must meet the following criteria:

They must have registered for, and used, at least some modules of interact-ABI-lity or social-ABI-lity, as verified by course records.They must have indicated consent at course enrollment to be contacted for further research participation opportunities related to the course.They must have provided informed written consent to participate in the interview. For users who have an ABI, capacity to consent will be determined during a video call with a qualified speech-language pathologist according to our adapted consenting process protocol that includes relevant questions adapted from the University of California, San Diego, Brief Assessment of Capacity to Consent instrument [55]. People with ABI without the ability to respond correctly to all 5 questions presented using supported communication strategies, as outlined in Multimedia Appendix 11 [55], will be excluded from the study.They must be aged ≥18 years.They must have adequate English proficiency to participate in the study without the aid of an interpreter, with functional reading skills in English.

There are no restrictions on any other factors (eg, gender, clinical experience, or geographical location) for interview participants who have used interact-ABI-lity and social-ABI-lity. Where possible, variation in these factors is preferred to obtain a purposive, maximum variation sample of user experiences of the interventions.

#### Inclusion and Exclusion Criteria for Users of convers-ABI-lity

Interviews will be conducted with all 10 people with ABI and their 10 communication partners who have completed the pilot version of convers-ABI-lity, as well as the 5 clinicians delivering the intervention. Participants with ABI must meet the following criteria:

They must have had a definite moderate-severe ABI at least 6 months previously based on the Mayo Classification Scheme [56] (at least one of the following: loss of consciousness of 30 minutes or more, posttraumatic amnesia lasting ≥24 hours, worst Glasgow Coma Scale total score in the first 24 hours of <13, or evidence of a significant brain imaging abnormality). People with a non–traumatic brain injury (restricted specifically to the etiologies of stroke, hypoxic injury, brain tumor, poisoning, and infection) will also be eligible to participate.They must have been discharged or partially discharged from hospital and be able to spend time at home on a regular basis.They must have significant social communication skills deficits (either self-identified or identified by a usual communication partner).They must have insight into their social communication skills deficits.They must be aged 18-70 years.They must have adequate English proficiency for completing assessment tasks without the aid of an interpreter.They must have functional reading skills in English.They must have a communication partner with whom they interact regularly who is willing to participate in the research interviews and training program.

The exclusion criteria for participants with ABI are as follows:

Aphasia of a severity such that it prevents any participation in conversation.Severe amnesia, which would prevent participants from providing informed consent, as evaluated using the University of California, San Diego, Brief Assessment of Capacity to Consent instrument [55].Dysarthria of a severity such that it significantly reduces intelligibility during conversation, as evaluated by the researcher.Drug or alcohol addiction, which would prevent participants from reliably participating in sessions.Active psychosis.Co-occurring degenerative neurological disorder, more than one episode of moderate-severe ABI, or premorbid intellectual disability.

Family members, friends, or paid support workers participating in the study must meet the following criteria:

They must regularly interact with a person with ABI (ie, at least once a week). This person with ABI must have had the ABI at least 6 months previously.They must have known the person with ABI for at least 3 months.They must not have sustained a severe ABI themselves.They must be aged ≥18 years.

Speech-language pathologists delivering convers-ABI-lity must meet the following criteria:

They must be currently employed in a clinical speech-language pathology role.At least 20% of their caseload must comprise people with ABI.

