### Aims

In this study, formative evaluation of the implementation of the Social Brain Toolkit by end users in the community will be used to guide intervention development and implementation [37] to support these interventions to reach and meet community needs in a feasible, scalable, sustainable, and acceptable manner. Therefore, guided by domains of the NASSS framework [34,35], in this hybrid implementation-effectiveness study, we aim to answer the following implementation questions:

Who uses these interventions and what are their characteristics (domains 1 and 4)? What implementation strategies can be used to improve intervention reach?In what geographical locations and health care and social contexts are the interventions used (domains 3 and 5-6)? What implementation strategies can be used to improve intervention reach?Do users complete the interventions as intended (domain 4)? Why or why not? What implementation strategies can be used to improve intervention adherence and fidelity?How usable is the technology for those completing the interventions (domain 2)? What changes can be made to improve usability?What barriers, facilitators, and workarounds do users experience when completing these interventions (domains 1-7)? What strategies, facilitators, and workarounds can be used to improve future implementation?How satisfied are users with the interventions (domain 3)? What changes can be made to increase user satisfaction?What is the cost of delivering each web-based intervention, and how does this compare with face-to-face delivery (domain 3)?

We seek to determine intervention effectiveness as follows:

Do people who complete the interact-ABI-lity course have improvements in their self-efficacy and knowledge about communicating with people with ABI?Do people who complete the social-ABI-lity course have improvements in their self-efficacy and knowledge about communicating safely and successfully on social media?Do people who complete the convers-ABI-lity program have improved communication and quality-of-life outcomes?

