#### Interviews

Intervention usability and user experience and satisfaction will be formatively evaluated through interviews. The first 30 minutes of the 90-minute interview will involve a think-aloud [43] review of the user interface through screen sharing of the web-based platform. The think-aloud method is a robust and flexible research technique to test usability by providing valuable and reliable information of users’ cognitive processes while completing a task [43]. This think-aloud task will be followed by a 60-minute qualitative interview, with interview questions developed using the NASSS framework of digital health implementation [34] to prompt discussion of multiple issues within this time frame (see Multimedia Appendices 3-7 for interview protocols). We will conduct the interviews as soon as possible after a user’s completion of the course to facilitate recollection of the intervention experience. We will conduct the interviews individually and with communication partners, depending on participant preference and availability. Data collection will occur entirely on the web, with interviews conducted through secure videoconferencing on Microsoft Teams (Microsoft Corporation) software [44]. The interview will be audio and video recorded using the built-in recording functions of the videoconferencing platform. Interview recordings will be transcribed verbatim for analysis.

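### The convers-ABI-lity interviews, read literally, take in only dyads who completed, and no interview point is set for course users who stop, so the question of why users do not complete is answered weakly

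*Protocol article*

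**What the plan says.** Under Aims, the third implementation question reads "Do users complete the interventions as intended (domain 4)? Why or why not", and goes on to ask which strategies would improve adherence and fidelity. It covers all three interventions and is not limited to people who finish.

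**convers-ABI-lity.** The participant section for this program defines the user interviews as "all 10 people with ABI and their 10 communication partners who have completed the pilot version of convers-ABI-lity". Five clinicians who deliver the program are to be interviewed too. The section describes no interview with a dyad that withdraws.

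**interact-ABI-lity and social-ABI-lity.** Interviewees qualify if they "registered for, and used, at least some modules of interact-ABI-lity or social-ABI-lity", so completion is not required. The number is set by "A minimum of 5 users of the social-ABI-lity course", and likewise for interact-ABI-lity, to be invited. Maximum variation is sought where possible. The examples given are gender, clinical experience and location.

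**Timing.** The Interviews section gives one rule: "We will conduct the interviews as soon as possible after a user’s completion of the course". The stated purpose is recall. No time point is given for a user who stops part-way.

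**The concern.** The guiding framework is named for nonadoption and abandonment, and the study wants user-identified strategies to shape the next version of the toolkit. People who finish have, by definition, got past whatever stopped the others. If the interview evidence comes mainly from them, barriers that lead to abandonment are likely to be under-represented, and strategies drawn from the interviews may be aimed at the wrong obstacles. The Strengths and Limitations section mentions analytics, sample size and self-report, but not this selection.

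**Working it through.** The plan states no figure for this point, so the check sets the sections side by side and then gives an illustration.

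**1. Scope of the question against scope of the sample.**
- The third question under Aims asks about completion and its reasons, for users in general. The fourth, on usability, is expressly limited to those completing. The authors therefore mark a completer-only question when they want one, and the third carries no such limit.
- convers-ABI-lity users: 10 people with ABI and 10 partners, conditioned on completion. First-hand accounts from dyads who stop: none described.
- convers-ABI-lity clinicians: 5, not conditional on a dyad's completion, but second-hand on reasons for stopping.
- The two courses: partial users are eligible, but have no interview time point and no reserved place.

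**2. Other sources that bear on the question.**
- All course users in the sample frame enter the survey and analytic data.
- Free-text survey answers are coded to the framework (Analysis, Qualitative).
- Descriptive statistics are stratified by completion (Analysis, Quantitative).
- Exit surveys: Participant Enrollment reports 8 exit surveys and 6 completions for interact-ABI-lity. With one survey per user, 8 − 6 = 2, so at least two appear to come from users not recorded as completers. The appendix title also describes exit surveys as for all users.

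Analytics and stratified tables show whether and when people stop. The reasons must come from free text and interviews.

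**3. Would chance supply non-completers in the two courses?** Assume five interviewees drawn at random from eligible users, with final completion rate c. The probability of no non-completer is c^5:
- c = 0.25: 0.25^5 = 0.1%
- c = 0.50: 0.50^5 = 3.1%
- c = 0.80: 0.80^5 = 32.8%

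If the timing sentence were applied in practice as a gate, the probability would be 100% whatever c is. The final c is not known.

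**4. Illustration of what is lost.** Assume a barrier met by 60% of non-completers and 10% of completers, with independent interviewees. Neither rate is in the article.
- Five completers all miss it: 0.9^5 = 0.590.
- Three completers and two non-completers all miss it: 0.9^3 × 0.4^2 = 0.729 × 0.16 = 0.117.
- Varying the completer rate: at 5%, 0.95^5 = 0.774 against 0.95^3 × 0.16 = 0.137; at 20%, 0.8^5 = 0.328 against 0.8^3 × 0.16 = 0.082.
- For convers-ABI-lity the sample is larger. With ten completing dyads, each counted once, 0.9^10 = 0.349. With twenty independent individuals, 0.9^20 = 0.122.

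**The case against.** The strongest case against is that completers are not the only informants. In two of the three interventions anyone who used some modules may be interviewed, and the timing sentence is about recall, not eligibility. Surveys and analytics cover all course users, and the quantitative tables already split by completion. That stands, and it rules out several stronger readings:

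- *The study cannot answer why users do not complete.* A reader might infer this, but partial-user interviews, clinician interviews, free text and stratified analytics all contribute.
- *Exit surveys come only from those who reach the end.* The 8 surveys against 6 completions and the appendix title point the other way, and the appendix itself is not shown.
- *Only 6/85 = 7.1% complete, so abandonment is 93%.* The count was taken on July 13, 2021, 11 days after data collection began on July 2, in a 6-month frame. Most of the other 79 may simply not have finished yet.
- *Five interviews miss a key barrier 59% of the time.* This needs assumed rates and five completers. The eligibility rule does not impose such a sample, and five is a minimum. For convers-ABI-lity the same 10% rate gives 12% to 35%.

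It can also be said that the convers-ABI-lity wording is loose and means the whole pilot cohort. That is possible. However, only one participant had been recruited at submission, so completion by all ten was still uncertain, and the literal text conditions on it. If the whole cohort is meant, correcting the phrase costs nothing.

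Finally, detailed sampling quotas may sit in a fuller protocol. That is fair for the quota. It does not explain a stated sample that is narrower than the stated question.

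**Conclusion.** The point holds in a limited form. For convers-ABI-lity, the interview sample as written excludes the people best placed to say why they stopped. This rests on reading the completion phrase literally. For interact-ABI-lity and social-ABI-lity, eligibility and timing do not fit together: a partial user may be interviewed but has no defined moment for it, and including such users is left to chance. There the reasons for stopping are studied weakly, not omitted.

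The size cannot be stated from the article, because neither completion rates nor barrier rates are known. The contrast of 59% and 12% shows the direction and possible scale under assumed rates, and nothing more. Whether satisfaction ends up overstated is plausible but not shown. The change is worth making because it serves a stated aim at little cost, but the study does not fail without it.

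**What to change.** 1. In the convers-ABI-lity participant section, replace the condition of having completed with all enrolled dyads who start the program, and offer the interview at completion or at withdrawal.
2. In the Interviews section, add a time point for consenting interact-ABI-lity and social-ABI-lity users who have been inactive for a set period, so that timing agrees with the eligibility rule.
3. Name completion status as a maximum-variation factor, with a minimum number of non-completers, for example 2 of the minimum 5 per course.
4. Report the qualitative findings by completion status, as is already planned for the descriptive statistics.

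Course users' email addresses and consent to research contact are collected at registration, and course records already verify use, so no new data system is needed. The cost is lower acceptance among people who stopped, and hence somewhat more invitations. The total number of interviews need not rise.

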### Ethics

This research has received ethical approval from the University of Technology Sydney (UTS) Health and Medical Research Ethics Committee (ETH21-6111) to conduct interviews with users of social-ABI-lity and interact-ABI-lity. The UTS Health and Medical Research Ethics Committee has also ratified (ETH21-5899) an approval by the Western Sydney Local Health District Human Research Ethics Committee (2019/ETH13510) to conduct interviews with users of convers-ABI-lity and collect demographic and web analytic data for all 3 interventions.

Users of the interact-ABI-lity and social-ABI-lity courses provide their email addresses at registration and indicate whether they consent to participate in follow-up research related to these courses. Consenting users of the courses will be invited to provide informed written consent to participate in a follow-up interview using an accessible, lay-language participant information and consent form. To ensure informed consent, the form will be adapted with visual supports and explained through video call for people with ABI, outlining the full burden and risks of research participation. Screening for capacity to consent is described in the aforementioned inclusion criteria (Multimedia Appendix 11).

Participants with ABI and their communication partners will be paid for their interviews at the 2021 hourly rate recommended by Health Consumers New South Wales [57]. Reimbursement for people with ABI and their communication partners is viewed as critical to recognizing the value of their lived experience of ABI, caring, and health care. It also aims to minimize any undue burden of research participation. Potential participants will be advised of this arrangement in the participant information form to facilitate decision-making around any potential economic burden of participation.

### Ethical Approval

Ethical approval was received from the UTS Health and Medical Research Ethics Committee (ETH21-6111) on June 29, 2021, and the Western Sydney Local Health District Human Research Ethics Committee (2019/ETH13510) on June 11, 2021, with ratification by the UTS Health and Medical Research Ethics Committee (ETH21-5899) on June 29, 2021.

### Participant Enrollment

At manuscript submission on July 13, 2021, 85 participants had enrolled in interact-ABI-lity, with 85 completed entry surveys, 6 course completions, and 8 completed exit surveys. No interview data had yet been collected. Data collection for interact-ABI-lity commenced on July 2, 2021, and is expected to conclude on January 2, 2022, after a 6-month sample frame of analytics. By July 13, 2021, 1 participant had been recruited to participate in the convers-ABI-lity study, with no data yet collected. Data collection is expected to commence on July 26, 2021, and conclude on March 26, 2022. By July 13, 2021, no participant had been recruited to participate in the social-ABI-lity study. Data collection is expected to commence on December 1, 2021, and conclude on June 1, 2022, after a 6-month sample frame of analytics.

### Analysis and Findings

Data analysis will occur concurrently with data collection until mid-2022. Results are expected for publication during late 2022 and early 2023.

## Discussion

### A Dual Focus on Implementation and Effectiveness

As the global burden of ABI grows, our communities and health care system must find a scalable, feasible, acceptable, and accessible health care service delivery solution to address the psychosocial burden of this condition [1]. A concerted focus on implementation is essential to ensure the successful and sustained uptake of health interventions, without which even efficacious treatments have failed to be adopted, implemented, or sustained [29]. Implementation knowledge should include the perspectives of key stakeholders, while also leveraging existing implementation science theory and evidence, to ensure implementation success.

To this end, we have selected several theoretically informed implementation measures, in addition to measuring the effectiveness of the Social Brain Toolkit. As social-ABI-lity and interact-ABI-lity are educational interventions, their effectiveness will be determined through measures of increased knowledge as well as ecologically valid postintervention measures such as frequency of social media use and confidence communicating with people with ABI. For the CPT intervention of convers-ABI-lity, effectiveness is determined by similarly meaningful measures of quality of life and conversation. The complexity of real-world implementation will be captured using mixed methods, including surveys and interviews exploring user satisfaction and experiences of implementation. For example, our specific survey of whether users are from rural, regional, remote, or metropolitan areas will enable the implementation experiences of these populations to be compared. Given the web-based nature of the Social Brain Toolkit, implementation measures will also include web analytics to identify any need for targeted implementation adjustments or strategies to improve intervention use. As the Social Brain Toolkit comprises technological interventions, think-aloud methods will be used to explore technological usability and provide users with a direct feedback channel to improve user interfaces.

As a prospective study of the real-world implementation of the Social Brain Toolkit, this study will not occur in a closed environment that allows controlled, randomized testing of isolated implementation strategies. Instead, with a theoretical foundation in the real-world complexity of digital health implementation [34], we will measure a comprehensive range of qualitative and quantitative effectiveness and implementation outcomes, and provide a recorded timeline of implementation strategy development and deployment for the Social Brain Toolkit.

